## Abstract

**Background:**

The prevalence of overweight and obesity in children has at least doubled in the past 25 years with a major impact on health. In 2005 a prevention protocol was developed applicable within Youth Health Care. This study aims to assess the effects of this protocol on prevalence of overweight and health behaviour among children.

**Methods and design:**

A cluster randomised controlled trial is conducted among 5-year-old children included by 44 Youth Health Care teams randomised within 9 Municipal Health Services. The teams are randomly allocated to the intervention or control group. The teams measure the weight and height of all children. When a child in the intervention group is detected with overweight according to the international age and gender specific cut-off points of BMI, the prevention protocol is applied. According to this protocol parents of overweight children are invited for up to three counselling sessions during which they receive personal advice about a healthy lifestyle, and are motivated for and assisted in behavioural change.

The primary outcome measures are Body Mass Index and waist circumference of the children. Parents will complete questionnaires to assess secondary outcome measures: levels of overweight inducing/reducing behaviours (i.e. being physically active, having breakfast, drinking sweet beverages and watching television/playing computer games), parenting styles, parenting practices, and attitudes of parents regarding these behaviours, health-related quality of life of the children, and possible negative side effects of the prevention protocol. Data will be collected at baseline (when the children are aged 5 years), and after 12 and 24 months of follow-up. Additionally, a process and a cost-effectiveness evaluation will be conducted.

**Discussion:**

In this study called 'Be active, eat right' we evaluate an overweight prevention protocol for use in the setting of Youth Health Care. It is hypothesized that the use of this protocol will result in a healthier lifestyle of the children and an improved BMI and waist circumference.

**Trial registration:**

Current Controlled Trials ISRCTN04965410

## Background

### Childhood overweight and obesity

The prevalence of overweight and obesity among children has at least doubled over the past 25 years, especially in socially disadvantaged and specific ethnic subgroups [1-6]. In the Netherlands, in 2003 the prevalence of overweight (obesity included) among boys and girls aged about 5 years was 12.8% and 17.5%, respectively, compared with 5.2% and 8.6%, respectively, in 1980 [7].

Adverse health effects of obesity in children are: type 2 diabetes, hypertension, high cholesterol levels, apnoea during sleep, psychosocial problems and a lower quality of life [8-12]. Being overweight or obese as a child increases the risk of becoming an overweight or obese adult [13], and is associated with increased morbidity and mortality [13-17]. Therefore, prevention of childhood overweight and obesity is important. To prevent and curtail the increase of overweight and obesity in children, evidence-based prevention programs are needed.

### Preventing childhood overweight and obesity

Studies have suggested that the methods for prevention of overweight and obesity in childhood are family-based intervention programs that include personal advice about a healthy lifestyle and counselling behavioural changes. Such programs should focus on a combination of inducing healthy nutritional behaviour (i.e. having family breakfast daily and reducing intake of sweet beverages) and reducing sedentary behaviour (i.e. inducing being physically active and reducing watching TV/playing computer games) [18-21]. The parents' role is of particular importance for the behaviour of children, especially among young children. Parents directly determine the physical and social environment of children, and indirectly influence behaviour and habits through socialization processes and modelling [22,23]. It is also recommended that more attention should be given to long-term sustainability and incorporating of interventions in daily practice [20].

The Netherlands has a unique system for the maintenance of the health of children, i.e. the Youth Health Care (YHC) system. All children (0–19 years) are monitored by a nation-wide program at set ages. This program is offered free of charge by the government; participation is voluntary. The attendance rate is 95%. During the YHC check-ups the growth of each child is measured [24]. In 2005 a consensus-based protocol was developed to be applied in the YHC setting for the prevention of overweight and obesity in children aged 0 to 19 years [25]. The Municipal Health Services (MHSs) are preparing the implementation of this prevention protocol; however, before wide-scale implementation an effect evaluation of the protocol is needed.

### Objectives

The first YHC check-up during school age is at 5–6 years: an important moment to consider the prevention of overweight. The aim of the study 'Be active, eat right' is to assess the effectiveness of the prevention protocol among children with overweight. The design of the study is described below.

#### The study hypotheses

The hypotheses of the study are that, after two years of follow-up, compared with the control group the overweight children in the intervention group will:

- have reduced BMI and waist circumference

- more frequently have family breakfast on a daily basis, and consume less sweet beverages

- spend more time being physically active and less time watching television/playing computer games

We apply a cluster design with YHC teams (physician, nurse and assistant) as the unit of randomisation. Randomisation at the individual level (i.e. the level of the children) may lead to contamination of the control group [26]. The outcome measures of the study (BMI, waist circumference, and levels of inducing/reducing overweight behaviours) are performed at the individual level. The follow-up measures will be compared between the intervention and control group, taking into account the baseline values.

## Methods and design

### Study design

This cluster randomised controlled trial is conducted in the Netherlands among children aged about 5 years and their parents, who are invited by the MHSs for a regular preventive health check. The YHC teams that perform the check consist of a physician, a nurse and an assistant; they form the unit of randomisation. The randomisation code was developed using a computer random number generator in SPSS to select random permuted blocks (specified allocation ratio 1:1). The block lengths were 4 or 6, depending on the number of YHC teams that participate per MHS. Within the MHSs an even number of YHC teams were randomly allocated to the two study arms: an intervention and a control group. The teams in the intervention group offer the prevention protocol to parents of overweight children, and in the control group the teams offer usual care to these parents. The effects of the prevention protocol will be evaluated after two years of follow-up by comparing the outcomes of BMI and waist circumference of the overweight children with those of the children in the control group, taking into account the baseline values of these measures [20,27]. Data collection started in September 2007 and will continue until August 2010. The Medical Ethics Committee of the Erasmus Medical Centre Rotterdam approved the study protocol (reference number MEC-2007-163).

### Study procedure

A few weeks before the regular preventive health check is scheduled, all parents receive information about the study 'Be active, eat right' at home by mail and are invited to provide written informed consent for participation in the study. In addition, all parents are invited to complete a two-page questionnaire to measure data on demographic factors, overweight inducing/reducing behaviours (i.e. being physically active, having breakfast, drinking sweet beverages and watching television/playing computer games), their attitudes regarding these behaviours, and the health-related quality of life of their children. With this information a non-response analysis can be performed.

During the preventive health check, the YHC teams register the measures of weight, height and waist circumference of the children, calculate the BMI, and classify all children as normal weight, overweight or obese according to the international age and gender specific cut-off points of BMI [27]. In the control group whenever a YHC team detects a child with overweight, they apply usual care. In general, this implies giving basic information to the parents during the regular preventive health check about the importance of good nutrition and physical activity.

In the intervention group, the subgroup of parents of overweight children are offered up to three additional structured lifestyle counselling sessions, according to the prevention protocol. During these sessions the focus is on four behaviours, i.e. being physically active, having breakfast, drinking sweet beverages, and watching television/playing computer games [28]. These particular behaviours were chosen based on a literature review reporting on the most promising elements to prevent overweight [25]. During the counselling sessions, parents receive personal advice about a healthy lifestyle and are motivated for and assisted in behavioural change.

At the end of the regular preventive health check, the subgroup of parents with overweight children (in both groups) are invited to complete an additional questionnaire. This questionnaire provides more specific data about the baseline levels of overweight inducing/reducing behaviours, attitudes of parents regarding these behaviours, and the health-related quality of life of the children.

### Participants

#### Municipal Health Services and Youth Health Care teams

The managers of the MHSs, managers of the YHC department, and managers of the department of health education of all 37 MHSs in the Netherlands were informed about the study by mail and were contacted by the researchers by telephone in the first half of 2007. From the 37 MHSs, 9 volunteered to participate in the study. Of the remaining MHSs, 3 did not meet the inclusion criteria (i.e. MHSs should have YHC teams that had not used the prevention protocol before), 25 MHSs had other reasons not to participate (e.g. a recent or upcoming merger of MHSs). Of the 9 participating MHSs, a total of 44 YHC teams were willing to participate in the study. When a professional worked in more than one YHC team, the team that invited the most children for the health check during the school year 2007/2008 was selected for participation, and the other team was excluded from participation. At the start of the study no major changes were expected in the composition of the participating teams. The participating teams cover both urban and rural regions in the Netherlands. Prior to the start of the study, the research group arranged meetings to explain the procedure of the study and to instruct the participating YHC professionals.

#### Children and their parents

The study population consists of the subgroup of children with overweight according to the international age and gender specific cut-off points for BMI. Parents and children will be excluded from analysis if the children have chronic health problems that may influence the outcome measures. In order to participate the parents should have at least basic Dutch language skills. The study design and participant flow are shown in Figures 1 and 2.

**Figure 1 F1:**
[figure not shown]
**Flow chart of the design of the study**.

**Figure 2 F2:**
[figure not shown]
**Flow of the clusters and participants through the trial**.

### Intervention

The prevention protocol (see appendix) is based on theories and models of behavioural change, i.e. the ASE model, a theoretical model of exercise habit formation, the Precaution Adoption Process Model, the Elaboration Likelihood Model, the stages of change model, and motivational interviewing techniques [29-34]. During the regular preventive health check, when a child in the intervention group with overweight is detected, the parents are offered up to three additional structured lifestyle counselling sessions to promote overweight-preventing behaviours. Prior to the start of the study, the YHC professionals in the intervention group received training in a non-directing guiding style as part of the prevention protocol [35]. The YHC professionals assess whether the parents are motivated to participate in this counselling, and will make use of a motivational interview approach if needed [35]. The three additional structured lifestyle counselling sessions are offered to parents with intervals of 1, 3 and 6 months after the regular preventive health check. The content of each visit depends on the stage of behavioural change that the parents are in [33]. The purpose of the sessions is to make parents aware of the overweight of their child, to provide information about overweight and its consequences, and to motivate the parents for and assist them in behavioural change. Materials that are used during the sessions are: a form for the YHC professional to assess the behaviours that should be targeted within the family, and diaries on energy intake and expenditure to be completed by the parents. Table 1 shows the guidelines for the four target behaviours for children at the age of about 5 years. The YHC professional and the parents together draw up a family-oriented action plan aiming at the promotion of physical activity and outdoor playing time, having family breakfast daily, consuming less sweet drinks and/or limiting watching television/playing computer games (Table 2) [25]. A pilot study has established the feasibility and acceptability of the prevention protocol [36].

**Table 1 T1:** Guidelines used during counselling sessions regarding the four target behaviours for children aged 5 years.

**Behaviour**	**Guideline**
Being physical active	- At least 1 hour each day
	- Moderate intensity (outdoor playing, walking, cycling or doing sport)
Having breakfast	- Daily
	- In the family setting
Drinking sweet beverages	- Not more than 2 glasses per day (of soft drinks, fruit juices, sports/energy drinks, sweetened milk/yoghurt drinks or tea with sugar)
Watching television/playing computer games	- Not more than 2 hours per day (watching television and playing computer games combined)

### Measurements

#### Primary outcomes

##### Body measurements

Standardised methods are used to measure weight, height and waist circumference of all children. The YHC professionals received training in measuring the waist circumference of the children and all use the same type of measuring tape (SECA 200) provided by the researchers. BMI is calculated using weight in kilogram divided by squared height in metres. The YHC professionals received a calculator with instructions on how to calculate BMI. At baseline the YHC professionals classify the children into groups of normal weight, overweight or obese, according to the age and gender-specific cut-off points for BMI as published by the International Obesity Task Force (IOTF) [27,37]. After two years of follow-up the anthropometric measures will be repeated.

#### Secondary outcomes

##### Four target behaviours

In the questionnaire (2 pages) and the additional questionnaire booklet (including questions from SQUASH [38], CHQ-PF28 [39] and SDQ [40]) parents report (for weekdays and weekend days) the following:

- the frequency and duration of physical activity and outdoor playing time of their children

- how often their children have breakfast

- the intake of sweet beverages of their children

- the frequency and duration of inactivity of their children due to watching television and/or playing computer games

Data on parenting styles, parenting practices and attitude of the parents concerning the four target behaviours are assessed. Examples are: behaviour of the parents themselves, family rules about watching television/playing computer games, and availability at home of sweet beverages and breakfast products. After 12 and after 24 months of follow-up a questionnaire to assess this data will be repeated.

Other characteristics that will be taken into account include:

- demographics: gender, ethnicity of the children and parents, educational level of the parents, household and family composition, and neighbourhood characteristics (i.e. can children play safely outside; presence of busy roads, etc.)

- self-reported weight and height of the parents themselves

- participation in weight-management programs other than those used in the present study

- general health of the children (measured with the 28-item Child Health Questionnaire (CHQ-PF28; [39])

- health-related quality of life, and emotional/behavioural problems of the children [40]

- indicators of negative side effects (i.e. worry, stigmatization and lower self-esteem related to the weight of the children, and development of relative underweight [20])

### Sample size

Sample size was calculated taking into account the intra-cluster correlation coefficient (ρ = 0.1), the number of clusters (44), the expected prevalence of overweight children in the study population, the standard deviation (SD), expected effect (a difference in mean), and the power of the study (80%). With a participation of 50%, an expected prevalence of overweight children of 9% and a loss-to-follow-up of 30%, at least 1,1301 children (and their parents) should be invited by the YHC teams to participate in the study to have a final sample of about 356 overweight children (178 in both the intervention and control group). Assuming a SD of BMI to be 1.0 kg/m^2 ^[36], a difference in mean BMI of 0.35 kg/m^2 ^between the children in the intervention group and the children in the control group can be established under the assumptions mentioned above. Assuming an SD of the average number of hours per day of watching TV, video, DVD and playing computer games combined to be 60 minutes per day [36,41,42], a difference of 20 minutes per day can be established.

### Statistical analysis

The aim of the study is to assess the effectiveness of the prevention protocol among children with overweight. An intention-to-treat analysis will be applied [43]. Multi-level analyses will be applied because of the three-level structure of the study, i.e. correlation of the repeated observations within a participant and the correlation of the observations of participants within a YHC team [26,44]. Linear multilevel analysis will be applied for continuous outcome variables and logistic multilevel analysis for dichotomous outcome variables [44]. Biometric and behavioural outcomes of the children at age 7 years will be analysed with independent variables: intervention or control group, gender, age, socio-economic status, ethnicity, weight of the parents, and baseline levels of the outcome variables. Interaction effects of gender, social disadvantage and ethnic background with the effect of the prevention protocol will be explored.

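### Teams were randomised within Municipal Health Services, but the stated analysis model has no Service term; if outcomes still differ between Services after adjustment, the primary linear analyses lose some precision

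*Protocol article*

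**What the plan says.** **Randomisation.** The abstract describes "44 Youth Health Care teams randomised within 9 Municipal Health Services". The Study design section gives permuted blocks with "specified allocation ratio 1:1" and adds: "The block lengths were 4 or 6, depending on the number of YHC teams that participate per MHS". It continues: "Within the MHSs an even number of YHC teams were randomly allocated to the two study arms". MHS is therefore the stratum within which the arms were balanced, at team level.

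**Analysis.** The Statistical analysis section specifies multilevel models, linear for continuous and logistic for dichotomous outcomes. The correlations to be modelled are the "correlation of the repeated observations within a participant and the correlation of the observations of participants within a YHC team". The independent variables are "intervention or control group, gender, age, socio-economic status, ethnicity, weight of the parents, and baseline levels of the outcome variables". MHS is not among the levels and not among the covariates.

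**The concern.** Balancing the arms inside each MHS means that differences between MHSs largely cancel when the arms are compared. The true variance of the treatment estimate falls accordingly. A model without MHS does not recognise this. It assigns the between-MHS variance to the team random effect and carries it into the standard error of the treatment effect.

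Any error is therefore on the cautious side: intervals too wide, a test below its nominal level, and power given away. At stake is efficiency on the two primary outcomes, in a trial with 44 randomised units and about 8 analysed children per unit.

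**Working it through.** **Inputs** (Protocol article, Sample size): 44 teams, so 22 per arm; intra-cluster correlation 0.1; 356 analysed children, 178 per arm; SD of BMI 1.0 kg/m²; difference 0.35 kg/m²; power 80%. Alpha and sidedness are not among the stated inputs.

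**The plan's own figure.** Children per team: m = 356/44 = 8.09. Design effect: 1 + (8.09 − 1) × 0.1 = 1.709. Effective number per arm: 178/1.709 = 104.2. SE of the difference: √(2/104.2) = 0.1386. Then 0.35/0.1386 = 2.53. Under the normal approximation power is 81.1% for a one-sided 5% test and 71.4% for a two-sided one. The stated 80% is reproduced only one-sided.

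**Layout of the strata (inferred).** If each MHS supplied one block of 4 or 6 teams, let b be the number of MHSs with 6. Then 4(9 − b) + 6b = 44, so b = 4: five MHSs with 4 teams and four with 6. Residual degrees of freedom on team means are 44 − 2 = 42 without MHS and 44 − 9 − 1 = 34 with it.

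**SE inflation.** The variance of a team mean is 0.1 + 0.9/8.09 = 0.2112. Let s be the share of the 0.1 that lies between MHSs. This share is an assumption, because the documents give none. With balance inside each MHS, the variance that reaches the treatment contrast is proportional to 0.1(1 − s) + 0.9/8.09. The ratio to the full variance is:

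- s = 10%: 0.2012/0.2112 = 0.953, so the SE is overstated by a factor 1/√0.953 = 1.02
- s = 25%: 0.1862/0.2112 = 0.882, factor 1.06 to 1.07
- s = 50%: 0.1612/0.2112 = 0.763, factor 1.14

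**Simulation.** This used team means in the layout above, equal team sizes, no covariates, a two-sided 5% t-test and 20,000 runs per row. It compared the model without MHS to the model with MHS as a fixed effect.

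| Share between MHSs | True SD of estimate | Model SE without → with | Type I error without → with | Power at 0.35 without → with |
|---|---|---|---|---|
| 0% | 0.138 | 0.138 → 0.138 | 5.0% → 5.0% | 69.4% → 68.9% |
| 10% | 0.136 | 0.138 → 0.135 | 4.8% → 5.2% | 69.5% → 70.4% |
| 25% | 0.130 | 0.138 → 0.130 | 4.0% → 5.2% | 70.7% → 74.5% |
| 50% | 0.121 | 0.138 → 0.121 | 2.7% → 4.9% | 72.3% → 80.4% |

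The simulated SE is too large by about 0%, 2%, 6% and 14%, in line with the formula. It was not materially too small in any row. The break-even share, where the gain in precision pays for the 8 degrees of freedom, lies between 0% and 10%.

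**The case against.** The strongest objection is that the loss is conditional. Nothing in the documents says how much outcomes vary between MHSs. At a share of zero, adding MHS slightly lowers power. This stands, and it is why the point is worded conditionally.

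Second, the power figures above ignore the covariates in the Statistical analysis section. Baseline outcome, socio-economic status and ethnicity may explain part of any MHS difference, and they reduce residual variance in general. As an illustration, assume a baseline correlation of 0.5 or 0.7, with half the residual team variance between MHSs. At a residual intra-cluster correlation of 0.1, power moves from about 85% to 90% (correlation 0.5) or from 96% to 98% (correlation 0.7). At a residual intra-cluster correlation of 0.02, the gain is under one point and the SE is overstated by about 4%. This also stands: the gain in the planned model is probably smaller than in the table.

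Third, the blocks balance numbers of teams, not numbers of overweight children. With unequal team sizes the MHS differences cancel largely, not wholly.

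Fourth, the article is a summary, and a fuller analysis plan could carry the term. That is possible. But this section does not simply stay silent: it sets out both the levels and the independent variables, and the randomisation stratum is in neither.

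A reader might also infer that the omission hurts a trial already below its stated 80% power. The documents do not support that. The shortfall appears under a two-sided 5% test, which the Sample size section does not specify, whereas a one-sided 5% test gives 81.1%. The MHS point does not depend on that question.

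**Conclusion.** The stated model leaves out the factor within which teams were randomised. The direction of the effect is clear: in the linear models for BMI and waist circumference, any residual between-MHS variance makes the SE too large and the test conservative. The size is unknown. It runs from nothing to an SE overstated by about 14% as the assumed share goes from 0% to 50%. The matching change in unadjusted two-sided power is from a loss of about 0.5 points to a gain of about 8, and probably less once baseline is in the model.

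A reader might infer that the results would be biased or the false-positive rate raised. Neither follows: the treatment estimate in the linear models is unbiased and the error is conservative. Nor do the documents show that power is certainly lost, since that needs between-MHS variance they do not report. The SE argument also does not carry over directly to the logistic models, where omitting MHS shrinks the odds ratio as well and the loss shows as power. This is a modest improvement in efficiency at little cost, not a flaw that threatens validity.

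**What to change.** State in the Statistical analysis section that MHS, as the randomisation stratum, enters the models comparing the arms and that the team random intercept stays.

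- **Linear models (BMI, waist circumference, continuous behaviours):** MHS as a fixed effect (8 indicators), with small-sample degrees of freedom for the treatment effect, about 34.
- **Logistic models:** MHS as a fixed effect where events allow, or as a random intercept where they are sparse. With about 356/9 = 40 children per MHS, eight indicators could leave empty cells for an uncommon outcome such as relative underweight.

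No new data are needed, because MHS membership is known for every team. If MHS explains nothing, the linear models give up 8 degrees of freedom (42 to 34) and about 0.5 points of power. The logistic models need a prespecified rule for choosing between the two forms.
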